### Study endpoints

The primary endpoint of the study is the gastrointestinal function-related quality of life 90 days after surgery, as assessed by the Gastrointestinal Quality of Life Index (GIQLI) total score [26].

Secondary endpoints ascertained during interventional study phase.

GIQLI total score 30 days after surgery.GIQLI subscales 30 and 90 days after surgery: symptoms (e.g. diarrhea, flatulence and constipation), physical functions, emotions and social function subscale.Changes in GIQLI total score and sub-scales from pre-surgical visit to day 30 and 90.Low Anterior Resection Syndrome (LARS) Score at day 90 after surgery.Further quality of life total and sub-scales (EQ-5D-5 L, EORTC QLQ-C30, and EORTC QLQ-CR29) 30 and 90 days after surgery and their changes from pre-surgical visit to day 30 and 90.Fatigue scale (EORTC-FA12) and sub-scales at day 90 after surgery.Anxiety (GAD-7) at day 90 after surgery.Cost-effectiveness (costs per prevented diarrhea case) and cost-utility of the intervention (costs per quality adjusted life-year (QALY) gained, as assessed with the EQ-5D-5 L).Emergence of multidrug-resistant organisms (MDRO) until day 90.Rate of physician-documented infections (bloodstream infection (BSI), catheter-related BSI, pneumonia, surgical site infections, intra-abdominal infections, and urinary-tract infections) until day 30 and day 90.Rate of self-reported infections (upper and lower respiratory tract infections, gastro-intestinal tract infections, bladder infections, wound infections, other infections and episodes with high fever (≥ 38 °C)) until day 30 and day 90.Total rate of infection until day 30 and day 90.Antibiotics use (Yes/No and number of days) until day 30 and day 90.Rates of post-operative complications, defined as the following 4 clinical events: Initiation of antibiotic or antifungal treatment, surgical revision, new mechanical ventilation, sepsis or death until day 90.Time from CRC surgery to hospital discharge.Number and length of re-hospitalizations until day 90.Changes in the gut microbiome composition until day 30 and day 90.Concentration changes of biomarkers of inflammation and immune function in serum samples collected prior surgery and 90 days after surgery (89 proteins of the combination of the OLINK^®^ Target 48 Cytokine panel and the OLINK^®^ Target 48 Immune Surveillance panel, including, for example, interleukin-6 as well as biomarkers of systemic inflammatory response (C-reactive protein (CRP), mGPS (modified Glasgow prognostic score), HS_mGPS (high-sensitive mGPS), NLR (neutrophil-to-lymphocyte ratio), PLR (platelet-to-lymphocyte ratio), LMR (lymphocyte-to-monocyte ratio), SII (systemic immune-inflammation index), PNI (prognostic nutritional index), and NPS (neutrophil-platelet score))).Concentration changes of metabolomic biomarkers (pre-defined selection of amino acids, fatty acids, and bile acids measured with high accuracy with targeted LC-MS/MS and the total metabolome measured with untargeted LC-MS/MS, which has lower accuracy) in fecal and plasma samples collected prior surgery and 90 days after surgery.

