### Study visits

Table 2 gives an overview on the study visits and more details follow in text below the table.

**Table 2 Tab2:** Study visits of the LEONORA study

Study visit	Time point	Intervention(s) / Procedure(s)
Pre-surgery visit	Day − 13 prior surgery to day of surgery	Informed consent, randomization, 1st questionnaire, 1st fecal sample (or rectal swab) and 1st blood sample.
Post-surgery visit	Day 1–3 post surgery	Handing out of trial medication and patient diary. Start of treatment as soon as liquid diet is being tolerated for 12 weeks (84 days).
Continuous monitoring for appearance of clinical events and compliance	Day 1 – Hospital discharge	Screening for clinical events (antibiotic/antifungal treatment, surgical revision, ventilation, sepsis or death), and monitoring of regular intake of study medication daily until hospital discharge. If a clinical event is detected, information will be documented in the eCRF.
Day 30 visit	Day 28–49 post surgery	2nd questionnaire and 2nd fecal sample.
Day 90 visit	Day 87–108 post surgery	End of trial. 3rd questionnaire, 3rd fecal sample, 2nd blood sample, and collection of filled patient diary.
Month 6 follow-up visit	Day 183–218 post surgery	4th questionnaire and 4th fecal sample. Collection of data on hospitalizations, infections, cancer treatments, cancer incidence/re-occurrence and vital status at authorities and/or general practitioners/oncologists.
Year 1 follow-up visit	Day 365–400 post surgery	5th questionnaire and 5th fecal sample. Collection of data on hospitalizations, infections, cancer treatments, cancer incidence/re-occurrence and vital status at authorities and/or general practitioners/oncologists.
Year 2 follow-up visit	Day 730–765 surgery	6th questionnaire. Collection of data on hospitalizations, infections, cancer treatments, cancer incidence/re-occurrence and vital status at authorities and/or general practitioners/oncologists.

*Abbreviations:*
*eCRF* electronic Case Report Form

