Incompliance: Defined as intake of trial drugs on less than 80% of the treatment days (i.e., < 67 days) as documented in the patient diary. If no patient diary was sent back to the coordinating center, this also counts as incompliance.Late completion of the day 90 questionnaire: Defined as > 115 days after surgery.Use of probiotic product in addition to the study medication (i.e., any time between post-surgery and day 90 visit).Late noticed false inclusion in the trial (inclusion criteria not fulfilled or exclusion criterion was present).

All secondary endpoints with a continuous scale will be analyzed with the same statistical methods as described for the primary endpoint above, with a linear regression model adjusting for center and the baseline value of the endpoint (if accessed). The dichotomous secondary endpoints will be tested with a logistic regression model or Cox proportional hazards regression model (depending on the nature of the endpoint) adjusted for center. In addition, a generalized estimating equation (GEE) model will be applied for all outcomes that have been repeatedly assessed.

The following a priori defined subgroup analyses will be conducted (The definition of pre-operative is “Assessed at pre-surgery visit,” and the definition of peri-operative is “Ascertained between pre-surgery visit and day 90 visit”):

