Age (< 65 / ≥ 65 years).Sex (female/male).Pre-operative cancer stage (I or II / III / IV).Tumor location (left colon / right colon/rectum).Pre-operative frailty (Non-frail / pre-frail / frail, as assessed with FRAIL scale [27])Post-operative stoma (no/yes, on day 30 only / yes, on day 30 and 90).Peri-operative antibiotic treatment (no (except single shot) / yes (additional to single shot)).Long-term post-operative antibiotic treatment (< 10 / ≥ 10 days).Adjuvant chemotherapy and/or radiotherapy (no/yes).Post-operative chemotherapy (no/yes, but not in week prior day 90 questionnaire date / yes, and in week prior day 90 questionnaire date).Post-operative radiotherapy (no / yes, but not in the week prior to the day 90 questionnaire date / yes, and in the week prior to the day 90 questionnaire date).Pre-operative GIQLI score (≤ median / > median).Pre-operative physical activity (≤ median / > median recorded with the Rapid Assessment of Physical Activity questionnaire (RAPA) [33]).Pre-operative alcohol consumption (Abstinent/ Alcohol consumption ≤ median / Alcohol consumption > median by grams of ethanol per week).Pre-operative smoking (current smoker / current non-smoker).Pre-operative Healthy Lifestyle Score (0–2 / 3–5 points [32])Pre-operative BMI (< 23 / 23–30 / > 30 kg/m²).Pre-operative cachexia (yes/no, definition of Blum et al. based on current BMI and weight loss in the last 6 months [35])Weight change from pre-surgery visit to day 90 questionnaire (≤ median / > median ∆BMIpct).Post-operative dietary fiber intake (≤ median / > median recorded with the validated FiberScreen 18-item food frequency questionnaire at day 90 [34])

Because of the multiplicity of tests for subgroup and secondary outcome analyses, all results except for the primary endpoint will be regarded as exploratory and not confirmatory.

No interim analyses are planned.

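### Eight of the 20 listed subgroups are defined by information arising after randomisation, so treatment contrasts within them are open to selection bias, most clearly for the two antibiotic items

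*Protocol article*

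**What the plan says.** Table 2 (Study visits) places randomisation at the pre-surgery visit: "Informed consent, randomization, 1st questionnaire" are all done there, between day −13 and the day of surgery. Trial medication starts on day 1 to 3 after surgery and runs for 84 days.

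The Statistical analysis plan section states: "The following a priori defined subgroup analyses will be conducted". It defines peri-operative as "Ascertained between pre-surgery visit and day 90 visit", a window that covers the whole treatment phase. Among the 20 subgroups are "Long-term post-operative antibiotic treatment" (below 10 days versus 10 days or more) and "Weight change from pre-surgery visit to day 90 questionnaire" (split at the median).

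The Study endpoints section lists as a secondary endpoint "Antibiotics use (Yes/No and number of days) until day 30 and day 90". Starting an antibiotic is also one of the events in the post-operative complication endpoint. The Background cites meta-analyses in which pro- or synbiotics reduced infections and shortened antibiotic use.

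The only caveat on the subgroups is that, because many tests are done, everything except the primary endpoint is exploratory.

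**The concern.** Randomisation makes the arms comparable within any group defined by a variable that treatment cannot have changed. If treatment does change the grouping variable, that protection is lost.

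Suppose synbiotics spare the milder cases from needing antibiotics. The synbiotic patients who still receive them are then sicker on average than the placebo patients who do. The spared patients join the no-antibiotic group and make it sicker on average than its placebo counterpart. Both strata can then show an apparent disadvantage for an inert treatment, or hide part of a real benefit. Fixing the cut-points in advance does not turn such a variable into a baseline characteristic.

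At stake is how the exploratory tables are read: a reader could take a stratum difference as a treatment effect, or a gap between strata as effect modification.

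**Working it through.** **Step 1: count and sort.** I took the plan's pre-operative labels at face value. Twelve of the 20 subgroups are then baseline variables. The other eight are:

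| Subgroup | Do the documents give reason to expect a treatment effect on it? |
|---|---|
| Peri-operative antibiotics (window to day 90) | Yes: secondary endpoint, and shorter use cited in the Background |
| Antibiotic days, <10 / ≥10 | Yes, same grounds |
| Weight change to day 90 | Possible, not documented |
| Fibre intake at day 90 | Possible, not documented |
| Stoma at day 30 only / days 30 and 90 | Persistence possible, not documented; creation at the index operation precedes the first dose |
| Adjuvant chemo- and/or radiotherapy | Weaker; no expected effect stated |
| Post-operative chemotherapy, split by week before day-90 questionnaire | Weaker |
| Post-operative radiotherapy, same split | Weaker |

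**Step 2: planning figures.** From the Sample size estimation section: means 77.0 and 72.5, SD 9.9, two-sided 0.05, power 80%. The two-sample t-test needs 76.95, so 77 per group and 154 in total; 154/0.75 = 205.3, so 206. The plan's figures reproduce, and the point does not depend on them. They supply the scale: SD 9.9 and difference 77.0 − 72.5 = 4.5.

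**Step 3: illustrate the bias.** The inputs other than the SD are assumptions, since the documents give no antibiotic rates and no link between severity and GIQLI.

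- Latent severity L is standard normal in both arms.
- GIQLI has SD 9.9 and correlation −ρ with L, with ρ = 0.3 or 0.5. Treatment has no effect on GIQLI in anyone.
- The probability of antibiotics is logistic in L with slope 1.5. The intercept is set per arm to give 40% under placebo and a lower rate under synbiotics.
- Spurious difference in stratum s = −ρ × 9.9 × (mean L in s under synbiotics − mean L in s under placebo).

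Numerical integration gives mean L at a 40% rate of 0.640 (antibiotics) and −0.427 (none), and at a 20% rate of 0.906 and −0.227. For ρ = 0.5:

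- antibiotics: −0.5 × 9.9 × (0.906 − 0.640) = −1.32
- no antibiotics: −0.5 × 9.9 × (−0.227 + 0.427) = −0.99

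| Placebo vs synbiotic rate | No antibiotics, ρ 0.3 / 0.5 | Antibiotics, ρ 0.3 / 0.5 |
|---|---|---|
| 40% vs 40% | 0 / 0 | 0 / 0 |
| 40% vs 35% | −0.15 / −0.25 | −0.18 / −0.29 |
| 40% vs 30% | −0.30 / −0.50 | −0.36 / −0.60 |
| 40% vs 25% | −0.45 / −0.74 | −0.57 / −0.94 |
| 40% vs 20% | −0.59 / −0.99 | −0.79 / −1.32 |

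Simulations of the same model with 2,000,000 patients scatter slightly around these values (to −1.36 in the last cell), hence the rounded range of about −0.1 to −1.4. The overall difference between arms is zero throughout.

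**Step 4: a second model, for the ≥10-day item.** Assume instead that L above a threshold means 10 days or more, with 30% under placebo. At rate p, with z the upper-p normal quantile and φ the normal density, mean L above the threshold is φ(z)/p. At 30% this is 1.159 and at 15% it is 1.554, so for ρ = 0.5 the difference is −0.5 × 9.9 × (1.554 − 1.159) = −1.96. That is the extreme, with the rate halved. At 25% versus 30% the ≥10-day stratum shows −0.33 to −0.56, and at equal rates zero.

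**The case against.** Most of the case on the other side concerns how far the point reaches.

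**Not every contrast is shown to be biased.** A reader might infer that all eight contrasts are biased. The documents do not support that: bias of this kind needs treatment to shift the grouping variable, and they give grounds for that only for antibiotics. A reader might also infer that several of the eight are trial endpoints; only the two antibiotic items are. This stands, and the point is worded accordingly.

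**The size is small next to noise.** With 77 analysed per arm and 40% versus 20%, the subgroup standard errors are 9.9 × √(1/61.6 + 1/46.2) = 1.93 without antibiotics and 9.9 × √(1/15.4 + 1/30.8) = 3.09 with them. The worst cell in each stratum is then about half a standard error (0.99/1.93 = 0.51; 1.32/3.09 = 0.43), which lifts a nominal 5% false-positive rate to about 7 to 8%. Both strata move in the same direction, so the spurious gap between them is only 0.79 − 0.59 = 0.20 to 1.32 − 0.99 = 0.33 points in the logistic model. Adjustment for baseline GIQLI would also absorb any severity already visible at baseline. This stands, and limits the weight of the point.

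**The results are declared exploratory.** True, and nothing confirmatory is touched. But the label is given for multiplicity. It does not address selection, which does not shrink with sample size or pooling.

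**Some tables are clinically useful.** Therapy in the week before the questionnaire and current stoma status describe the patient's condition when GIQLI is completed. This stands as a reason to keep the items as description. It does not justify presenting them as effect modifiers.

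**Conclusion.** The point holds in a limited form. Eight of 20 subgroups use post-randomisation information, and treatment contrasts within them are open to selection bias. For the two antibiotic items the plan conditions on its own secondary endpoint, one it has reason to think treatment reduces. For weight change, fibre intake and stoma persistence the bias is possible but undocumented. For chemo- and radiotherapy and for stoma creation the case is weaker.

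The size is an illustration that rests on assumed antibiotic rates, severity correlation and model form. Under the logistic model it is about −0.1 to −1.4 points, at most roughly 30% of the planned 4.5 (1.32/4.5 = 29%; 1.4/4.5 = 31%). The harsher threshold model for the ≥10-day item reaches about −2.0 when the rate is halved. It is zero if treatment leaves antibiotic use unchanged.

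The primary analysis and sample size are unaffected. The plan should be changed because doing so is cheap and the exploratory label does not cover this problem.

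**What to change.** Restrict treatment-effect (effect-modifier) subgroups to variables fixed before randomisation or, where suitable, before the first dose. In particular, take the two antibiotic items off that list. Twelve subgroups remain.

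Move the eight items to a separate descriptive section. Suggested wording: *The following characteristics arise after randomisation and may be influenced by treatment. They will be described by arm. Comparisons between arms within their categories are not protected by randomisation; they will not be interpreted causally or as evidence of effect modification.* The items need not be deleted, and stoma status at days 30 and 90 need not be replaced by another variable.

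The cost is a wording change and the loss of some planned exploratory contrasts. No visit, measurement or sample size changes. Recruitment began in September 2025, so the change should be dated and made before unblinding.

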#### Questionnaire data

Patients will undergo a structured assessment of their quality of life at 6 different time points throughout the study period. Assessment will be performed using the standardized GIQLI, EQ-5D-5 L, EORTC QLQ-C30 core questionnaire and EORTC QLQ-CR29 module [26–29].

The pre-surgery visit questionnaire additionally contains questions about socio-demographic factors and frailty (FRAIL scale [30]). To keep this first questionnaire short, questions on school education, social network (Duke-UNC FSSQ-5 ([31]), co-morbidity, time since the CRC diagnosis, smoking history, and family history of CRC were added to the day 30 questionnaire.

In the day 90, month 6 and month 12 questionnaires, lifestyle questionnaires were added (smoking, alcohol consumption, physical activity, nutrition as well as height and weight for body mass index calculation) using standardized instruments (HEALTHY life-style score [32], Rapid Assessment of Physical Activity questionnaire (RAPA) [33], and the FiberScreen 18-item food frequency questionnaire to assess the amount of fiber in the diet [34]).

Furthermore, questions related to cancer treatments (chemotherapy, radiotherapy, additional surgery), hospitalizations (dates, length and reason), infections (number, location, vaccinations), antibiotics use, and newly developed cancers or CRC reoccurrence (location, date) were added to all follow-up questionnaires from day 90 on.

The questionnaires will be scanned, the scanned information will be verified by visual inspection, and the data will be electronically stored in pseudonymized manner on secured servers in the coordinating center. Scanned information from the pre-surgery visit, day 30, and day 90 questionnaire, needed for the primary and secondary endpoint(s) during the interventional phase of the study, will be verified by two independent documentarists and disagreements will be resolved by inspection of the original questionnaire.

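### Four of the 20 planned subgroups are labelled pre-operative, but the protocol describes no pre-surgery collection of the variables that define them

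*Protocol article*

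**What the plan says.** The section Statistical analysis plan introduces the a priori subgroups with a definition: a variable is pre-operative if it was "Assessed at pre-surgery visit". The list that follows has 20 entries. Four of them are lifestyle variables carrying that label:

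- "Pre-operative physical activity (≤ median / > median recorded with the Rapid Assessment of Physical Activity questionnaire (RAPA) [33"
- "Pre-operative alcohol consumption (Abstinent/ Alcohol consumption ≤ median / Alcohol consumption > median by grams of ethanol per week"
- "Pre-operative smoking (current smoker / current non-smoker"
- "Pre-operative Healthy Lifestyle Score (0–2 / 3–5 points [32"

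The section Questionnaire data says where each instrument is placed. The pre-surgery questionnaire holds the quality-of-life scales plus socio-demographic and frailty questions. To keep it short, several topics, smoking history among them, were moved to the day 30 questionnaire. On lifestyle it says: "In the day 90, month 6 and month 12 questionnaires, lifestyle questionnaires were added (smoking, alcohol consumption, physical activity, nutrition", and it names the lifestyle score, RAPA and the FiberScreen questionnaire as the instruments used there.

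**The concern.** A subgroup variable has to exist at the time its label claims. On the schedule described, none of the four is recorded at the pre-surgery visit, so an analyst who follows the plan literally has nothing to split on. The obvious workaround is to take the day 90 values and keep the label.

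For activity, alcohol and the lifestyle score, that would mean splitting on values recorded in the same questionnaire as the primary endpoint, after randomisation, surgery and the full treatment period. How active patients are and how much they drink at that point may depend on how their gut feels, which is what the GIQLI measures, and so possibly on treatment. Within strata of such a variable the two arms are no longer comparable by randomisation. A reader told that the variable was pre-operative could not see this.

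**Working it through.** No arithmetic decides this point. The check compares the subgroup list with the data-collection schedule.

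**Step 1: count.** The list has 20 subgroup variables. Nine are labelled pre-operative: cancer stage, frailty, GIQLI score, physical activity, alcohol, smoking, Healthy Lifestyle Score, BMI and cachexia. The four lifestyle variables are 4 of 20, and 4 of those 9.

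**Step 2: first described collection.** Sources are Questionnaire data and Table 2.

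| Subgroup variable | Timing the label requires | First described collection | Window (days after surgery) |
|---|---|---|---|
| Physical activity (RAPA) | pre-surgery visit | day 90 questionnaire | 87–108 |
| Alcohol | pre-surgery visit | day 90 questionnaire | 87–108 |
| Healthy Lifestyle Score | pre-surgery visit | day 90 questionnaire | 87–108 |
| Smoking | pre-surgery visit | day 30 (history), then day 90 | 28–49, then 87–108 |

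None of the four meets the definition.

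**Step 3: other baseline sources.** The description of the pre-surgery visit mentions baseline quality-of-life scales and contact details. Table 2 adds only consent, randomisation and samples. The list of eCRF data has age, sex, weight, height, comorbidities, medication and cancer treatment, but no smoking, alcohol, activity or lifestyle score. By contrast, frailty and the GIQLI are in the first questionnaire, and weight and height for BMI are in the eCRF. Those labels hold.

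**Step 4: omission or contradiction?** The article states where the lifestyle block sits and that the first questionnaire was deliberately shortened. The same subgroup list also labels dietary fibre, measured by an instrument from that same block, as post-operative and taken at day 90. One block is therefore treated as post-operative for fibre and pre-operative for activity.

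**Step 5: timing against treatment.** Treatment starts on day 1–3 and lasts 84 days, so it ends by about day 87. The day 90 window opens on day 87. Day 90 values therefore come after the whole intervention, and day 30 values come during it.

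**Step 6: what is untouched.** The primary model uses centre and baseline GIQLI, and none of the four variables. The sample size reproduces: for a difference of 77.0 − 72.5 = 4.5 and SD 9.9, two-sided 0.05, exact t-test power is 79.5% with 76 per arm and 80.03% with 77, hence 154. Then 154 / (1 − 0.25) = 205.3, rounded up to 206.

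**The case against.** Four points can be made on the other side.

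*Smoking is different.* A reader might infer that all four variables are available only together with the primary endpoint. That is not so for smoking: a history is taken at day 30 and, depending on wording that is not shown, may yield pre-surgery status by recall. The article already counts education as baseline data for imputation although school education is asked at day 30. This stands. Smoking still falls outside the stated definition, but it is the mildest case.

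*Missing values.* A reader might add that the 25% planned dropout would lack these variables. The documents do not support this as a further loss in the main subgroup analyses of the primary endpoint. Dropout is defined as having no day 90 GIQLI, and the main analysis imputes covariates only, so those participants (206 − 154 = 52 on the planning figures) have no outcome there anyway. Extra missingness could matter in the sensitivity analysis with imputed GIQLI, or for endpoints obtained without that questionnaire.

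*The bias is conditional.* Nothing says that day 90 values will stand in for pre-operative ones, and the recall period of the day 90 items is not shown. This stands. What is certain is that the subgroups cannot be formed as defined; bias follows only if the substitution is made.

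*The lists may be condensed.* The pre-operative cachexia subgroup needs weight loss over the previous six months, which neither the eCRF list nor the description of the first questionnaire mentions. Either those lists are incomplete or a fifth subgroup has a similar gap. This slightly lowers certainty. For the lifestyle items, however, the article goes beyond silence: it places them at later visits and explains why the first questionnaire is short.

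**Conclusion.** The point holds as an internal contradiction between the definition and subgroup list in Statistical analysis plan and the schedule in Questionnaire data. It affects 4 of 20 subgroups: three are first measured at day 90, and one, smoking, at day 30.

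The size of any bias cannot be computed from the documents, and its direction is open. It would arise for activity, alcohol and the lifestyle score if day 90 values were analysed as pre-operative, and if treatment or gastrointestinal well-being influences them. Both conditions are assumptions. The verdict also assumes that the questionnaires contain what the article says they contain.

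A reader might take this for a defect that must be cured before the trial can be relied on. The documents do not support that: every result other than the primary endpoint is declared exploratory, and the primary analysis and sample size are unaffected. Minor to should-fix is the right grade. Timing is the reason to act soon: the first participant was included in September 2025, recruitment is planned over 2–3 years, and a value not measured before surgery cannot be measured later.

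**What to change.** Reconcile the two sections in one of three ways.

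- **(a) Collect at baseline.** Add short smoking, alcohol and RAPA items to the pre-surgery questionnaire for participants still to be enrolled, and restrict these subgroups to them. The article does not list the components of the lifestyle score, so anything else it needs would have to be added too. Cost: a questionnaire amendment, a slightly longer first questionnaire, and loss of participants enrolled since September 2025 from these subgroups.
- **(b) Relabel by actual time of measurement.** Call activity, alcohol and lifestyle score day 90 variables, as is already done for dietary fibre, and smoking status recalled at day 30, if the item allows it. State that the day 90 variables are not to be interpreted as baseline effect modifiers. Cost: a text change, and a weaker interpretation.
- **(c) Delete the four subgroups.** Cost: none in data collection; the questions go unanswered.

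Under any option, state that day 90 values will not be reported as pre-operative. While amending, confirm where the six-month weight loss for the cachexia subgroup is recorded.
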